## Abstract

Implementation of evidence-informed rehabilitation of the upper limb is variable, and outcomes for stroke survivors are often suboptimal. We established a national partnership of clinicians, survivors of stroke, researchers, healthcare organizations, and policy makers to facilitate change. The objectives of this study are to increase access to best-evidence rehabilitation of the upper limb and improve outcomes for stroke survivors. This prospective pragmatic, knowledge translation study involves four new specialist therapy centers to deliver best-evidence upper-limb sensory rehabilitation (known as SENSe therapy) for survivors of stroke in the community. A knowledge-transfer intervention will be used to upskill therapists and guide implementation. Specialist centers will deliver SENSe therapy, an effective and recommended therapy, to stroke survivors in the community. Outcomes include number of successful deliveries of SENSe therapy by credentialled therapists; improved somatosensory function for stroke survivors; improved performance in self-selected activities, arm use, and quality of life; treatment fidelity and confidence to deliver therapy; and for future implementation, expert therapist effect and cost-effectiveness. In summary, we will determine the effect of a national partnership to increase access to evidence-based upper-limb sensory rehabilitation following stroke. If effective, this knowledge-transfer intervention could be used to optimize the delivery of other complex, evidence-based rehabilitation interventions.

## 1. Introduction

Implementation of evidence-based stroke rehabilitation interventions improves patient outcomes [1,2]. Evidence-based therapies for the upper limb after stroke are recommended in clinical practice guidelines [3,4] and in international best-practice guidelines [5,6]. Yet, there is inconsistent access to and delivery of quality, evidence-based stroke rehabilitation, leading to suboptimal outcomes [3,7,8]. The need for and potential benefit of implementation interventions to promote the uptake of best-evidence rehabilitation are highlighted [9,10,11].

There are currently very few knowledge-transfer interventions of known effectiveness to facilitate practice change for complex interventions in stroke rehabilitation, and the certainty of the evidence is very low [11]. We developed an implementation intervention to drive behavior change in clinical and community settings [12]. The intervention is guided by the Theoretical Domains Framework [13,14,15], with translation strategies from the Behavior Change Wheel [16]. The intervention targets the delivery of science-based rehabilitation that requires knowledge and skill of the rehabilitation therapist, an application of knowledge translation that is virtually untested in the field of stroke rehabilitation [12].

Major evidence–practice gaps in stroke rehabilitation have been identified in addressing the loss of body sensation after stroke nationally [17] and internationally [18], contributing to poor arm use and reduced ability to return to previous life activities after stroke [19,20,21]. Impaired sensation is experienced by one in two stroke survivors [22,23,24,25]. This loss is beyond any reduction experienced with healthy aging [22,23]. As survivors of stroke report: “It is like the hand is blind” and “…I couldn’t really do daily stuff... I couldn’t hold anything, things were just dropping…so I had nothing, there was nothing there” [26]. Many learn non-use of their hand, leading to secondary problems and restricting return to valued activities and work [19,20,22,27]. In addition, upper limb sensory loss is a factor contributing to inferior results in rehabilitation outcomes [19,28,29,30], and adequate sensation is a prerequisite for full motor recovery of the paretic upper limb [31].

Despite the high prevalence and negative impact on function, it has been highlighted that loss of body sensations is a ‘neglected’ area of stroke rehabilitation [32]. Rehabilitation therapists often use a compensatory, rather than restorative, approach to somatosensory loss and recovery [17,18]. Yet, use of compensation potentially reinforces learned non-use of the limb with negative long-term consequences. In our national survey, less than half of healthcare professionals reported satisfaction with the treatments they were using, or confidence in their ability to treat somatosensory impairment after stroke, indicating a readiness to change practice [17]. Barriers to implementation of best-practice sensory rehabilitation identified by therapists include low therapist confidence; lack of skills; inconsistent access to resources; and reduced quality of therapy delivery [17,33].

The purpose of this study is to increase access to best-evidence rehabilitation of the upper limb and improve outcomes for stroke survivors. Our focus is on delivery of best-evidence somatosensory rehabilitation, given the evidence–practice gap identified nationally and internationally [17,18]. Specifically, we will use a knowledge transfer intervention to upskill therapists and deliver recommended best-evidence somatosensory rehabilitation to more survivors of stroke.

A neuroscience-based approach to rehabilitation of somatosensory impairment, known as SENSe (Study of the Effectiveness of Neurorehabilitation on Sensation) [34] (http://youtu.be/G9V3I30pn68; accessed on 2 October 2023), has been systematically developed and tested, consistent with the Medical Research Council Framework for the development and evaluation of complex interventions [35]. SENSe therapy has demonstrated efficacy across a series of studies [36,37], including a double-blinded randomized controlled trial [34], with reported improvements in somatosensory capacity [34] and performance of valued occupations [26]. Survivors of stroke report the positive experience and benefits of being involved in SENSe therapy, demonstrating acceptability of this therapy for this population [26]. SENSe therapy is recommended in clinical practice guidelines for stroke [3] and in best-practice International Standards for Arm Rehabilitation Post-stroke [5].

Skill and experience of the therapist may impact implementation and delivery of evidence-based complex interventions. This is particularly evident when service delivery requires a high level of skill from therapists [11,38]. Investigation of the impact of therapist experience on therapy outcomes is therefore warranted. Further, while evidence is growing about health outcomes from implementation interventions across various settings and health professional groups [11,39], there is a paucity of data on their cost-effectiveness to inform whether the investment of resources justifies the additional benefits that might be achieved. Therefore, this study will also investigate cost-effectiveness of the intervention.

We have created a partnership of survivors of stroke, clinicians, researchers, healthcare organizations, and policy makers to (i) increase access to evidence-based SENSe therapy delivered by therapists via a network of clinical practice settings and specialist SENSe therapy centers, and (ii) improve outcomes for survivors of stroke with somatosensory impairment of the arm/hand. The partnership is supported with a National Health and Medical Research Council Partnership grant from Australia (GNT 1134495), which has allowed us to create a centralized knowledge-translation hub and four specialist therapy centers.

Two complementary studies, SENSe Implement [12] and SENSe CONNECT (ACTRN12618001389291), are being undertaken to address the identified gap and achieve our overall aims. Together, the studies will permit investigation across different modes of delivery and skill levels of therapists and will involve approximately 100 therapists and 250 stroke survivors. The first study, SENSe Implement [12] (ACTRN12615000933550), focuses on testing the effectiveness of our knowledge-transfer intervention to change clinician behavior in existing rehabilitation services. Specifically, the aim is to determine whether evidence-based knowledge-translation strategies change the practice of occupational therapists and physiotherapists in the assessment and treatment of sensory loss of the upper limb after stroke to improve patient outcomes. This study is being conducted as a pragmatic, before–after study involving eight Australian healthcare networks and existing sub-acute and community rehabilitation services (see [12] for further details).

The second study detailed here is known as SENSe CONNECT (ACTRN12618001389291). The SENSe CONNECT study is designed to increase access to evidence-based SENSe therapy via specialist SENSe therapy centers and skilled therapists. Four new specialist SENSe therapy centers, across three states in Australia, are planned to complement and extend current services. This model of service delivery differs from the current practice model being tested in the SENSe Implement study. The focus for SENSe CONNECT is on increased access for survivors of stroke living in the community. We will create a centralized hub to lead the knowledge-translation intervention and provide upskilling of therapists. A network of specialist SENSe therapy centers and community of therapists will be linked with the hub to facilitate implementation and sustainability. Web-based resources will be developed to further support therapists and help sustain practice change. Some of the broader contextual aspects of implementation [40,41] will also be investigated in the SENSe CONNECT study, including impact of therapist expertise on outcomes and cost-effectiveness. The specific aims of the current SENSe CONNECT study are to

Increase access to evidence-based SENSe therapy delivered via a network of specialist SENSe therapy centers and skilled therapists.Improve outcomes for survivors of stroke with somatosensory impairment of the arm/hand (primary outcome—somatosensory function; secondary outcomes—performance of self-selected valued activities, arm use, and quality of life).Achieve high treatment fidelity for therapists in the delivery of upper-limb sensory rehabilitation following a tailored, evidence-informed knowledge-transfer intervention.Explore the association of the amount of therapist experience in SENSe delivery with outcomes for stroke survivors.Evaluate the cost-effectiveness of the knowledge-translation intervention in terms of the amount of improvement in SENSe therapy outcomes, i.e., somatosensory function, performance in valued activities, arm use, and quality of life.

## 2. Materials and Methods

### 2.1. Study Design

The overall knowledge translation study involves a centralized hub, 4 specialist SENSe therapy centers, and 11 healthcare networks to deliver evidence-based upper-limb sensory rehabilitation for stroke survivors. The SENSe CONNECT arm detailed here is a prospective, pragmatic knowledge-translation study, involving four specialist SENSe therapy centers and stroke survivors in the community. Inclusion criteria are broad to test broader treatment effectiveness, and therapy will be delivered using a within-participant wait list control design [42].

#### 2.1.1. Centralized Translation Hub

A centralized hub was created to lead the knowledge translation intervention and provide upskilling of therapists. This includes a multimodal approach to upskilling therapists [12], which is supported with a therapy training manual and a suite of training videos. Therapists are credentialled and treatment fidelity is monitored and supported using document audit and fidelity observations and feedback [43]. The network of specialist services and community of therapists will facilitate implementation and sustainability. Web-based resources have been developed (https://sensetherapy.net.au/; accessed on 2 October 2023) to further support therapists and help sustain practice change via a community of practice. An overview of the network of sites and centers involved is provided in Figure 1.

#### 2.1.2. Specialist SENSe Therapy Centers and SENSe CONNECT Protocol

Four specialist SENSe therapy centers have been set up to deliver SENSe therapy to stroke survivors across three states in Australia. The new specialist therapy centers are linked with healthcare networks and universities or research institutes. The SENSe therapy centers will permit delivery of therapy to stroke survivors living in the community. Therapy may be delivered at the center or in the client’s home.

Occupational therapists and physiotherapists skilled and credentialled in SENSe therapy will deliver SENSe therapy to stroke survivors across the specialist therapy centers, using a pragmatic, within-subject wait list design [42]. The wait list design will evaluate change in outcomes over a 6-week period of usual care not associated with SENSe therapy, compared to a 6-week period of SENSe therapy delivered by credentialled therapists. During the wait list phase, participants will receive usual care, which will be monitored. Upper-limb therapy will not be restricted for participants during the control wait list phase; rather, participants will receive ‘usual care’ conditions [44]. Consistent with an independent review and analysis of ‘usual care’ usually received in health services in Australia (based on national audit and knowledge-translation study), this will usually not involve specific sensory rehabilitation, such as SENSe therapy [44]. Participants may continue to receive usual care during the SENSe therapy intervention period. Our prior controlled clinical trials provide evidence that exposure to sensory stimuli alone and/or current usual care is not usually sufficient to affect clinically significant improvement in somatosensory function [34,36,37]. All services and usual care received will be monitored.

Stroke survivors attending specialist SENSe therapy centers will be assessed on four occasions: baseline (i.e., Assessment 1, A1); after 6 weeks of usual care (i.e., A2); after 6 weeks of SENSe therapy (i.e., A3); and at follow up, 12 weeks post A3 (i.e., A4). All participants attending SENSe therapy centers will receive SENSe therapy (10 sessions) over a 6-week period. Assessors for health outcomes of stroke survivors will be blinded to study design and timing of therapy delivery. Researchers and statisticians involved in the data analysis will also be blinded to study design and timing of therapy delivery.

SENSe therapists will not be blinded due to pragmatic reasons. It is planned that each therapist will deliver SENSe therapy to up to 12 stroke survivors. A secondary analysis will permit investigation of the association between stroke survivor outcomes achieved and the therapist’s amount of experience in delivering SENSe therapy. The study is approved by Austin Human Research Ethics Committee (HREC/18/Austin/153), and all experiments will be performed in accordance with the Declaration of Helsinki. Site-specific ethics approvals were also obtained. All participants will give voluntary informed consent.

Sample size: Stroke survivors—The SENSe CONNECT study design requires a within-subject, repeated measures analysis. The within-group analysis from the original SENSe randomized controlled trial (RCT) revealed a Cohen d of 0.366 for the somatosensory function outcome (repeated measures, small group *n* = 22/50; [34]). To achieve a within-group effect of d = 0.366 for a power of 0.8, a minimum sample of *n* = 61 is required. In the current study, the proposed sample size of *n* = 72 to 192 (i.e., 18 to 48 deliveries at each of the 4 centers) achieves this minimum and allows for dropout or poor recruitment. Assuming the variability in changes found in the SENSe RCT is replicated in the delivery of SENSe therapy, a maximum sample size of *n* = 192 will have a high degree of precision for estimating the effect size obtained within the SENSe therapy centers. The larger sample size will also facilitate generalizability of effect estimates to the broader target population of survivors of stroke living in the community. Therapists—At each specialist SENSe therapy center, it is planned that 3 or 4 therapists will each deliver SENSe therapy to 6 to 12 stroke survivors (i.e., 18 to 48 deliveries at each site; 72 to 192 across sites). A sample of 12 to 16 therapists was chosen to maximize replication across upskilled therapists while exploring the association between the amount of experience in delivery of SENSe therapy and therapy outcomes.

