### 2.4. Outcomes

Access to evidence-based sensory rehabilitation: The primary outcome is the number of complete deliveries of SENSe therapy at the SENSe therapy center by therapists credentialled in SENSe therapy. A delivery will be counted as complete if it meets the criterion of at least 7 sessions delivered with a stroke survivor.

Stroke survivors: The primary outcome is change in arm somatosensory function, pre–post SENSe therapy, across three somatosensory domains, measured using standardized, quantitative somatosensory measures and a normalized summary impairment index calibrated to normed age-matched performance [34,45]. The index will be derived from scores on the Tactile Discrimination Test [46], Wrist Position Sense Test [47], and functional Tactile Object Recognition Test [48]. Each of these quantitative measures assesses the person’s ability to discriminate different somatosensations; i.e., texture discrimination, wrist joint proprioception, and haptic object recognition of the upper limb. Comparable ranges of impairment from just noticeable to extreme impairment defined for each measure enable the normalization of the three test scales for comparison in clinical and research settings [45].

The following secondary outcomes will also be assessed: client-rated performance and satisfaction of valued activities, using the Canadian Occupational Performance Measure (COPM) [49] and clinician-rated performance on the same valued activities using the Performance Quality Rating Scale for Somatosensation after Stroke [50]; arm use, using Motor Activity Log-14 [51]; and health-related quality of life, using the Assessment of Quality of Life (AQoL-6D) [52]. See Table 1 for the schedule of study outcomes.

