Effect of SENSe therapy: We will evaluate the therapeutic gain in arm somatosensory function for stroke survivors (primary outcome) during the SENSe therapy phase compared to that of the usual care phase by estimating the mean within-person difference between the two trends and the associated 95% confidence intervals. The magnitude of change in arm somatosensory function under the two conditions will be calculated as a standardized effect size and compared to the benchmark effect size obtained in the original SENSe RCT (comparable cohort) [34]. Statistical estimates of change will be reported with 95% confidence intervals, and the extent of overlap across studies in these estimates of change will be described. Confidence intervals for the difference between mean change scores from the present and benchmarked study [34] will also be obtained. The analysis design will include the SENSe therapy center as a variable, to evaluate its potential systematic effect. Individual participant characteristics that may impact magnitude of therapeutic gain, such as age and time post-stroke, will be explored. Improvement in secondary outcomes, i.e., clinician-rated performance in valued activities, arm use, and quality of life, will also be evaluated pre–post therapy. Depending on verification of the normal distribution assumption, either a t-distribution or a bootstrapping method will be used to obtain the confidence interval. Maintenance of the intervention effect will be evaluated at the 12-week follow up (A4).

Treatment fidelity and behavior change: High fidelity delivery will be defined as a score of 80% or higher on the SENSe treatment fidelity checklists [43]. Audit data from treatment sessions will be independently summarized for each SENSe therapy treatment program delivered. The number of therapy deliveries achieving high treatment fidelity will be summarized. Pre- and post-implementation questionnaires of therapist knowledge, confidence, and ability to deliver SENSe therapy will be summarized and response tendencies will be examined using contingency tables, McNemar’s test, and graphical representation.

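### The 80% power and minimum of 61 rest on a within-group effect size that is not tied to the planned between-phase contrast, so 80% power at n = 72 is unsupported and probably not met

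*Protocol article*

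**What the plan says.** Three parts of the Protocol article bear on this.

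- **Sample size (section 2.1.2).** The study is described as needing a within-subject analysis: "The SENSe CONNECT study design requires a within-subject, repeated measures analysis". The effect size comes from the earlier SENSe RCT, whose within-group analysis "revealed a Cohen d of 0.366 for the somatosensory function outcome (repeated measures, small group" of 22 out of 50). Then: "To achieve a within-group effect of d = 0.366 for a power of 0.8, a minimum sample of" 61 is required. The planned 72 to 192 is said to be enough because it "achieves this minimum and allows for dropout or poor recruitment". The only statement on variability is conditional: "Assuming the variability in changes found in the SENSe RCT is replicated in the delivery of SENSe therapy".
- **Outcome (section 2.4).** "The primary outcome is change in arm somatosensory function, pre–post SENSe therapy, across three somatosensory domains". This is a single change, A2 to A3.
- **Design and analysis (sections 2.1.2 and 2.8).** "The wait list design will evaluate change in outcomes over a 6-week period of usual care not associated with SENSe therapy", and this is set against a 6-week SENSe phase. Section 2.8 evaluates the SENSe-phase gain "compared to that of the usual care phase by estimating the mean within-person difference between the two trends", with 95% confidence intervals.

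The sample-size text gives no alpha, no usual-care change, no SD for the difference between phases and no correlation between the two changes. It does not say which SD standardises 0.366.

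**The concern.** With assessments at A1, A2 and A3, the section 2.8 contrast is D = (A3−A2) − (A2−A1) = A3 − 2·A2 + A1. It differs from a single pre–post change in two ways.

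- **Spread.** A2 enters both changes with opposite sign. That pushes their correlation towards negative values and tends to make the SD of D larger than the SD of one change.
- **Size of effect.** D subtracts whatever is gained during usual care. A single pre–post gain does not.

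If 0.366 describes one change, the 80% attached to n = 61 does not carry over to D. The low end matters in practice. The limitations in section 3 expect the pandemic to affect deliveries of therapy and the recruitment and retention of therapists, so a final number near 72 is possible. Readers have been told that 72 is sufficient.

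**Working it through.** **Inputs.** d = 0.366, power 0.80, n = 61 and the range 72 to 192 are from section 2.1.2. Alpha is not given; two-sided 5% is assumed, in line with the 95% intervals in section 2.8. The usual-care gain is not given; zero is taken as the base case, with 10% and 25% of the SENSe gain also shown.

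**Step 1: the plan's own figure.** For a paired t-test with standardised effect d_z, power comes from the noncentral t with n − 1 degrees of freedom and noncentrality d_z·√n. With d_z = 0.366, n = 61 gives 80.3% power and is the smallest n to reach 80%. So 61 reproduces exactly. On the same basis n = 72 gives 86.5%. Falling from 72 to 61 is a loss of 11/72 = 15.3%.

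**Step 2: variance of the planned contrast.** Let VR = Var(D) / Var(one change).

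- Equal SDs of the two changes, correlation r between them: VR = 2(1 − r). Uncorrelated changes give VR = 2.
- Equal visit variances σ² and equal visit correlations ρ: Var(D) = 6σ²(1 − ρ) against 2σ²(1 − ρ), so VR = 3 (r = −0.5).
- First-order autoregressive visits: VR = 3 − ρ, between 2 and 3 for positive ρ.
- Usual-care change SD equal to k times the SENSe change SD: VR = 1 + k² − 2rk.

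**Step 3: power for D if 0.366 is per SD of one change and usual care yields no gain.** d_z(D) = 0.366/√VR.

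| VR | d_z(D) | n for 80% | Power at 61 | at 72 | at 192 |
|---|---|---|---|---|---|
| 1 | 0.366 | 61 | 80% | 87% | >99% |
| 1.25 (k = 0.5, r = 0) | 0.327 | 76 | – | 78% | – |
| 2 | 0.259 | 120 | 51% | 58% | 95% |
| 3 | 0.211 | 178 | 37% | 42% | 83% |

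Power at 72 is 80% when VR is about 1.20. With equal SDs that requires r of about +0.40, since 1 − 1.196/2 = 0.402.

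**Step 4: a usual-care gain of fraction f of the SENSe gain.** d_z(D) = 0.366(1 − f)/√VR.

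| f | Power at 72, VR 1 / 2 / 3 | Power at 192, VR 1 / 2 / 3 |
|---|---|---|
| 0.10 | 79% / 50% / 36% | 99.5% / 90% / 75% |
| 0.25 | 63% / 37% / 26% | 97% / 76% / 59% |

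**Step 5: if 0.366 is per raw-score SD instead.** For one change d_z = 0.366/√(2(1 − ρ)); for D with VR = 3, divide again by √3.

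| ρ between visits | n for 80%, one change | n for 80%, D | Power for D at 72 |
|---|---|---|---|
| 0.5 | 61 | 178 | 42% |
| 0.7 | 38 | 108 | 63% |
| 0.8 | 26 | 73 | 80% |
| 0.9 | 14 | 38 | 98% |

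**Step 6: precision.** In units of the SD of one change, the 95% half-width for D is t·√(VR/n). At 72 (t = 1.994) it is 1.994 × √(2/72) = 0.33 to 1.994 × √(3/72) = 0.41. At 192 (t = 1.972) it is 1.972 × √(2/192) = 0.20 to 1.972 × √(3/192) = 0.25. On the single-change reading, the effect to be detected is 0.366 in these units.

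**The case against.** The strongest reply is that section 2.1.2 never says 0.366 is a single pre–post change. Any paired effect size of 0.366 gives 61, including one for a difference between phases. Reproducing 61 therefore cannot show which contrast was used. This stands, and it rules out saying as fact that the stated power is not delivered. It does not supply the missing link: a within-group effect most naturally means one change, and nothing ties it to section 2.8.

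The variance ratios of 2 and 3 are also assumptions. If the usual-care change varies less than the SENSe change, the ratio falls; half the SD with no correlation gives 1.25 and 78% power at 72. Under a raw-score standardiser with visit correlation 0.9, power at 72 is 98%. So a reader might infer that the true minimum is 120 to 178 on the article's own effect size, but those figures come from added variance assumptions. The shared A2 makes the favourable ratios less likely, without excluding them.

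Section 2.4 words the primary outcome as the pre–post change, which fits the calculation. That is fair, but it moves part of the problem into a disagreement between sections 2.4 and 2.8 and does not support the power claim for the section 2.8 contrast.

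Whether 0.366 includes practice or natural gain cannot be told from this document. Section 2.1.2 expects usual care usually not to produce clinically significant improvement, which is not the same as zero change.

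Finally, section 2.8 is framed around estimates and intervals, and the upper end of the range is well powered if usual care yields no gain. Both are true, but the article still claims 80% power and still calls 72 sufficient.

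**Conclusion.** The point holds as a mismatch between the sample-size basis and the planned contrast. The arithmetic behind 61 is correct. What is unsupported is applying it to the difference between phases, and hence the assurance about 72.

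On the natural reading (0.366 per SD of one change, two-sided 5%, no usual-care gain), power at 72 is about 58% with uncorrelated changes of equal SD and about 42% with equal visit variances and correlations. The numbers for 80% are then 120 and 178, and power at 192 is 95% and 83%. Power at 72 stays near 80% only if the variance of the difference is at most about 1.2 times that of one change or, for a raw-score standardiser under equal visit correlations, if that correlation is about 0.8 or more. Any usual-care gain lowers these figures. So 80% power at the low end is unsupported and probably not met.

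Two stronger inferences should not be drawn. One is that a trial of 72 is more likely than not to be inconclusive: in the base case that fits a variance ratio of 3 (42% power) but not 2 (58%). The other is that a null result would stand as evidence of failed implementation: section 2.4 gives implementation its own primary outcomes, completed deliveries and treatment fidelity.

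**What to change.** - State one primary contrast for stroke survivors and word it the same way in sections 2.4 and 2.8.
- Say what 0.366 measures (one change or a difference between phases) and which SD standardises it. State alpha and sidedness.
- For the chosen contrast, report power and 95% interval half-width at 72 and 192. If it is the difference between phases, give explicit assumptions for the SD of A3 − 2·A2 + A1 and for the usual-care change, drawing the SD from repeated pre-treatment measurements in the earlier RCT if available.
- Remove or qualify the statement that 72 meets the minimum and leaves room for dropout.

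This is a text change to the sample-size paragraph and the outcome and analysis wording. It needs no additional participants. The cost is that the stated power at the low end will probably be less favourable.
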